### **Post-operative patient management**

A standardised therapy management with respect to enteral nutrition, mobilisation etc will be applied and documented in detail in the CRF.

On ICU volume replacement will be performed at the discretion of the attending physician. See “unauthorised concomitant medication”.

For the assessment of the second primary variable, time until fully on oral diet, it has to be assessed for a period of maximally 15 days. It will be assessed for each day (on the subsequent day) whether the patient receives parenteral nutrition. As soon as the patient is off parenteral nutrition and has taken nutrients via oral (not enteral) pathway at least three times that day no further recording of nutritional diet is required.

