|                               | 
<math>\alpha</math>1-MG, <math>\beta</math>-NAG, creatinine
 
 
o postoperative days 3 and 7: creatinine in serum
 
 
day +2 – day +15 maximal (i. e. as long as patient receives parenteral/enteral nutrition) on respective care unit (control on subsequent day for predecessor day)
 
 
▪ control of nutrition/diet: Is parenteral nutrition administered – Has the patient taken nutrients orally at least for three times that day.
 
 
3 months after surgery
 
 
▪ Health Related Quality of Life (HRQoL)
 
                                                                                                                                                                                                                                                                            |
| Duration of Study per Patient | 
Start of study: with randomisation
 
Treatment period (infusion of Investigational Products):
 
During surgery (guided by measurement of oesophageal Doppler)
 
End of study: Postoperative Day 15 or discharge from hospital whatever occurs first
 
Last evaluation of certain parameters will be 3 months post-surgery respectively when DRG data are available
                                                                                                                                                                                                                                                                                                                                                                                                                                                                                                                                                       |

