## **12 DEFINITION OF THE PRIMARY AND SECONDARY VARIABLES**

### **12.1 Primary Variable**

First primary endpoint: Intraoperatively required amount of HES (mLs) under target controlled volume replacement therapy.

Second primary endpoint: Time until fully on oral (solid) diet (days): Fully on oral (solid) diet is reached when no more parenteral and enteral nutrition is given and the patient has taken nutrients via the oral pathway for at least three times that day.

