**day +2 – day +15 maximal**

- control at subsequent day whether the patient receives or not parenteral nutrition. Control of nutrition is stopped when the patient does not receive any parenteral nutrition and is able to take nutrients via the oral pathway (not enteral) at least 3 times that day.

**3 months after surgery** (telephone call only)

- Health Related Quality of Life (HRQoL)

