## **15 DURATION OF STUDY AND STUDY SCHEDULE**

### **15.1 Duration of study per patient**

Start of study: with randomisation

Treatment period (infusion of Investigational Products):

During surgery (guided by oesophageal Doppler measurements)

End of study: Postoperative day 15 or hospital discharge, whatever occurs first

Last evaluation of certain parameters will be 3 months post-surgery respectively when DRG data are available.

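### The next-day diet check leaves the last study day without a scheduled check, and the rules for stopping the check do not match the definition of the second primary endpoint

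*Protocol*

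**What the plan says.** **Timing of the check.** Section 11 (Post-operative patient management) says of the second primary variable that "it has to be assessed for a period of maximally 15 days", and adds: "It will be assessed for each day (on the subsequent day) whether the patient receives parenteral nutrition". The synopsis visit schedule, in its block for days +2 to +15, gives the same rule: "control on subsequent day for predecessor day". Section 14.1, under the same day range, has "control at subsequent day whether the patient receives or not parenteral nutrition".

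**End of study.** Section 15.1, in line with the synopsis: "End of study: Postoperative day 15 or hospital discharge, whatever occurs first". It adds: "Last evaluation of certain parameters will be 3 months post-surgery respectively when DRG data are available". In section 14.1 the three-month telephone contact lists quality of life only, and no section assigns a diet question to it.

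**Stopping the check.**
- Synopsis: the check runs "as long as patient receives parenteral/enteral nutrition". The bullet beneath asks about parenteral nutrition and about three oral intakes.
- Sections 11 and 14.1: recording stops once the patient is off parenteral nutrition and takes food by mouth at least three times in the day.
- Section 12.1 (endpoint): neither parenteral nor enteral nutrition is given, and "the patient has taken nutrients via the oral pathway for at least three times that day".

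**The concern.** The endpoint is a date, and the date comes from a daily question put to the patient; section 12.5 names the CRF as the source for nutrition intake. If the question about a given day is asked on the following day, the question about the last study day falls after the study has ended for that patient. Someone who first meets the definition on day 15, or on an earlier discharge day, then has no scheduled check that dates the event.

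The stop rules raise a related problem. A check that ends on a condition weaker than the endpoint, or different from it, can end before the endpoint is reached.

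The SAP can decide how to rank a patient without a date. It cannot supply an observation that was not scheduled, so this has to be settled in the protocol and CRF.

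**Working it through.** **1. Count of days.** A check on day t describes day t − 1.

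- First check, day +2: describes day 1.
- Last check, day +15: describes day 14.
- Days covered: 1 to 14, that is 14 days against the 15 allowed in section 11.
- Day 15 would need a check on day 16, and a discharge day a check on the day after. Both fall after the end of study in 15.1.

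If the range +2 to +15 means the days described rather than the days of asking, the day-15 check still falls on day 16.

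**2. Other records of the last day.**

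- The synopsis lists time until full oral nutrition among gastrointestinal parameters measured daily from day +1 until reached or end of study, with no next-day lag. However, the visit lists from day +2 onward (synopsis and 14.1) name only auscultated bowel movement, start of enteral nutrition and first defaecation. They run to day +5 at most. The footnote to the 14.2 overview exempts only nutrition control from that limit.
- The 14.2 overview records parenteral nutrition to day 15 at most. It mentions neither enteral nutrition nor three oral intakes.

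So part of the last day's status is captured. A scheduled check of all three elements of 12.1 is not.

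**3. Stop rules applied to three patient states.**

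| State on a given day | Synopsis parenthesis | Sections 11 and 14.1 | 12.1 met? |
|---|---|---|---|
| Off all artificial feeding, fewer than three oral intakes | stop | continue | no |
| Off parenteral, still on enteral, three oral intakes | continue | stop | no |
| Off both, three oral intakes | stop | stop | yes |

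Each rule stops too early in one state, and it is a different state for each. None of the check questions asks about enteral nutrition.

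**4. Size.** Inputs from sections 16.2 and 16.4: two-sided alpha 5%, planning power 80%, 1.5 days' difference, effect size d = 0.698 (implied SD 1.5/0.698 = 2.15 days), 69 per group.

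Noether's formula for the Mann-Whitney test uses p = Φ(d/√2), with n = (1.960 + 0.842)² / [6(p − 0.5)²] per group and power = Φ(√(6n)·(p − 0.5) − 1.960).

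The plan's figures reproduce:
- d = 0.5: n = 68.5, so 69 (stated 69).
- d = 0.698: n = 36.5, so 37 (stated 37).
- d = 0.698, n = 69: power 97.06% (stated 97%).

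Now let a share f of each HES arm be undated and left out. The documents give no f, so it is an assumption.

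| f | n per group | Power |
|---|---|---|
| 2% | 67.6 | 96.8% |
| 5% | 65.5 | 96.3% |
| 10% | 62.1 | 95.5% |
| 20% | 55.2 | 93.1% |
| 40% | 41.4 | 84.7% |

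Power comes down to the planned 80% only when about 37 per group remain, that is f = 1 − 37/69 = 46%.

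**5. Sensitivity to where the times lie.** This is a simulation with assumed inputs: normal times rounded to whole days, SD 2.15, difference 1.5 days, 69 per group, undated patients left out. It moves the last datable day from 15 to 14.

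| Iso-oncotic mean (assumed) | Power, day 15 → 14 | Mean difference in days, day 15 → 14 |
|---|---|---|
| 10 days | 97.7% → 97.3% | 1.48 → 1.43 |
| 12 days | 95.1% → 91.0% | 1.31 → 1.15 |
| 13 days | 91.5% → 80.8% | 1.15 → 0.95 |

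If patients without a date by day 14 are instead ranked as longest, power stays at about 97% for all three means.

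**The case against.** **The last day is recorded elsewhere.** The synopsis measures time until full oral nutrition daily to the end of study, and parenteral nutrition is recorded to day 15. This stands to the extent that a reader should not infer that the last day's diet status is never recorded. It does not close the gap, because the visit lists do not carry that daily measurement past day +5, and the parenteral record covers one of the three elements in 12.1.

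**Nothing forbids a check on day 16.** True for a patient still in hospital. The check is unscheduled rather than excluded, and sites may handle it differently.

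**The synopsis parenthesis is loose wording that the body resolves.** Partly right: its own bullet asks about three oral intakes, which would serve little purpose if checking ended at weaning. But sections 11 and 14.1 still differ from 12.1 on enteral nutrition, and that difference lies within the body of the protocol.

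**Two stronger inferences fail.** A reader might conclude that affected patients drop out of the rank test. Section 16.5 says only that missing values are not imputed. It does not say whether a patient without a date counts as missing or is ranked last, and the SAP may properly settle that. A reader might also conclude that those affected are slow recoverers, so that the loss is selective. That holds for the day-15 group only. A patient who first meets the criterion on an early discharge day has recovered fast, and one weaned before eating three times a day may be at any stage.

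**Conclusion.** The point holds in a limited form. The next-day check and the end of study on day 15 or at discharge do not fit together: the last study day has no scheduled check, and the checks cover 14 days where section 11 speaks of up to 15. The rules for stopping the check disagree with each other and with 12.1, so recording can end before the endpoint is met.

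The gap from the check timing is at most one day per patient. Power would fall from about 97% to 95–96% if 5–10% of patients were undated and left out; both the share and the exclusion are assumptions. A loss of about 4 to 11 points appears only if undated patients are left out and the iso-oncotic mean is about 12 to 13 days, a figure the documents do not give. The case for changing the text is therefore cleaner ascertainment of a primary endpoint at little cost, not a threat to the trial's power.

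**What to change.** In the synopsis, section 11 and section 14.1:

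1. On the last study day (day 15 or the day of discharge), record that day's diet status on the day itself, or allow the final check on day 16 or the day after discharge. A same-day entry at discharge sees only the hours in hospital, whereas a check the day after sees the whole day. Choose one and apply it at all sites.
2. State whether day 15 is inside the assessment window.
3. Use one stop rule, namely the full criterion of 12.1, and remove the synopsis condition that ties the check to artificial feeding.
4. Ask about enteral as well as parenteral nutrition at each check.

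Cost: one extra CRF entry or one contact per patient, an enteral-nutrition item in the daily check, and matched wording in three places. Treatment is unaffected.

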#### **7.1.1 Primary Variable**

A multiple primary endpoint is defined which is “the intra-operative amount (in mLs) of colloidal volume replacement therapy during target directed volume replacement therapy” as the first primary endpoint and “days until fully on oral (solid) diet” as the second primary endpoint (full on oral diet is defined by the absence of parenteral and enteral nutrition and the patient is able to take oral nutrition for at least three times that day).

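### The daily diet check and its stop rule leave out enteral nutrition, which the second primary endpoint requires to be off, so the endpoint date can be recorded too early or lost

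*Protocol*

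**What the plan says.** **Definition.** Section 7.1.1 states that "full on oral diet is defined by the absence of parenteral and enteral nutrition" together with oral nutrition at least three times that day. Section 12.1 agrees: the endpoint is reached "when no more parenteral and enteral nutrition is given and the patient has taken nutrients via the oral pathway" at least three times that day.

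**Recording.** Section 11 (Post-operative patient management) sets out how this variable is assessed, for at most 15 days: "It will be assessed for each day (on the subsequent day) whether the patient receives parenteral nutrition". It then gives the stop rule, "As soon as the patient is off parenteral nutrition and has taken nutrients via oral (not enteral) pathway at least three times that day", from which point "no further recording of nutritional diet is required". Section 14.1 (day +2 to day +15) says the same: "Control of nutrition is stopped when the patient does not receive any parenteral nutrition" and can take nutrients orally, not enterally, at least three times that day. The synopsis visit schedule lists two daily questions. One asks whether parenteral nutrition is given; the other is "Has the patient taken nutrients orally at least for three times that day". In the Section 14.2 overview, the entry that runs to day 15 names parenteral nutrition only.

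**Other passages on the same data.**
- The synopsis list of efficacy variables has time until full oral nutrition measured daily until it is fulfilled or the study ends.
- The synopsis visit schedule keeps nutrition control open for as long as either parenteral or enteral nutrition is given.
- Section 11 says in general terms that the management of enteral nutrition is standardised and documented in the CRF.
- Section 14.1 lists the start of enteral nutrition, but not its end, among the gastrointestinal parameters for day +2 onwards, a block that ends by day +5.
- Section 16.5 states that missing values will not be imputed.

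**The concern.** A site that follows Sections 11 and 14.1 exactly collects two of the three facts needed to date a confirmatory endpoint, and may stop collecting before the third is true. The wording in brackets, oral and not enteral, does not repair this. It says which intakes count towards the three; it does not require enteral feeding to have ended.

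At stake is the date itself. The analyst could take the day the stop rule was met, which is earlier than the defined endpoint for the affected patients, or could apply Section 12.1 and have no date for them. A later analysis plan can choose between these, but it cannot restore observations that sites were told not to make. The same dates also feed the pooled-variance check of the second endpoint after the pilot phase (Section 16.4).

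**Working it through.** **Step 1. Set the passages side by side.**

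| Place | Parenteral off | Enteral off | At least 3 oral intakes |
|---|---|---|---|
| 7.1.1 and 12.1, definition | required | required | required |
| 11, stop rule | required | not mentioned | required |
| 14.1, stop rule | required | not mentioned | required |
| Synopsis, daily questions | asked | not asked | asked |
| 14.2, entry to day 15 | listed | not listed | not listed |

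The omission recurs in every place that tells sites what to record, so it is not a slip in one sentence.

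**Step 2. Follow one patient.** On day *s* the patient is off parenteral nutrition, takes nutrients orally three times and still receives enteral feeds. Enteral feeding ends on day *e*, later than *s*. The stop rule is met on day *s*; the endpoint is reached on day *e* at the earliest. Using *s* dates the endpoint at least *e* − *s* days early. Applying the definition leaves no date, because diet recording ended on day *s*. A tube-fed patient who does not yet take nutrients orally three times in a day does not meet the stop rule and goes on being recorded.

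**Step 3. Reproduce the planning figures.** Section 16.4 assumes a 1.5-day difference and an effect size of 0.698, so the SD is 1.5 / 0.698 = 2.15 days. By Noether's formula for the Mann-Whitney test, with p = Φ(0.698/√2) = 0.689:
- n per group for 80% power = (1.960 + 0.842)² / [6 × (p − 0.5)²] = 36.5, so 37.
- Power with 69 per group = Φ(√(6 × 69) × (p − 0.5) − 1.960) = 97.1%.

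Both match the stated 37 and 97%. The recording gap does not alter them.

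**Step 4. What misdating could do.** The protocol gives neither the share of patients affected nor the lag, so the actual effect cannot be computed. Its form can be shown. Let f₆ and f₁₀ be the affected shares in the 6% and 10% HES arms and L the mean lag in days. If the stop day is used, each arm's mean falls by f × L, and the recorded difference (6% minus 10%) is 1.5 − (f₆ − f₁₀) × L.

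With L = 3 days and the shares below, all assumed, and the SD held at 2.15, power at 69 per group by the normal approximation is Φ(difference / (2.15 × √(2/69)) − 1.960):

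| f₁₀ | f₆ | Recorded difference (days) | Power |
|---|---|---|---|
| 20% | 20% | 1.5 | 98% |
| 20% | 30% | 1.2 | 91% |
| 10% | 30% | 0.9 | 69% |
| 30% | 10% | 2.1 | over 99% |

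The first row is the unbiased reference on this approximation, which runs slightly above Noether's 97%. The table shows direction only and is not an estimate.

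**Step 5. The strict reading.** If affected patients have no date, a share of 10% to 30% leaves 69 × 0.9 = 62 down to 69 × 0.7 = 48 per group, still above the 37 needed for 80% power. The loss of numbers is therefore not the main problem. The problem is that missingness depends on feeding status, which is part of the outcome.

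**The case against.** The best defence is that the protocol does not rely on the stop rule alone. The synopsis follows time until full oral nutrition daily until fulfilment, and Section 12.5 lists it as a CRF item. The synopsis window stays open during enteral feeding. Section 11 promises detailed CRF documentation of enteral nutrition management. The CRF is not shown and may hold the day enteral feeding ended.

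This defeats one inference a reader might draw, that nothing is recorded after the stop rule is met. It does not remove the mismatch. The synopsis variable has no criterion of its own, so a site would reasonably apply the rule in Sections 11 and 14.1. The wider window still comes with only two questions. The CRF statement names neither a daily item nor an end date. The result is instructions that conflict, and the gap stays open.

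Other strong readings also fail:
- *Every patient still tube-fed when parenteral nutrition stops is misdated.* Only those also taking nutrients orally three times a day are.
- *The gap could remove a large part of the planned 1.5 days.* A shift in one arm's mean is not a shift in the difference between arms, and the affected share is unknown.
- *Centres feed differently, so the error varies by centre.* The protocol describes postoperative care and enteral nutrition management as standardised, and randomisation is stratified by centre.
- *The error falls on the slow recoverers who carry the treatment contrast.* No passage supports this.

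It is also fair to say that this endpoint is tested only if the first is significant, and that its planned power is high.

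**Conclusion.** The point holds as a contradiction between the endpoint definition and the instructions for recording it. As written, the plan allows the date of a confirmatory endpoint to be recorded too early, or to be missing, for patients who take nutrients orally three times a day while still enterally fed. The textual finding rests on no assumption.

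Its numerical effect cannot be derived from the documents. Equal affected shares and lags in both HES arms leave the mean difference unchanged; unequal ones could shrink or inflate it. Whether the true date could be recovered depends on CRF content that the protocol does not specify. The correction should be made in the protocol, because it concerns what is observed and not how it is analysed.

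The word solid in the endpoint's name is a smaller matter. Section 12.1 itself reduces the term to the three conditions and none of them tests for solid food, so on this the daily check follows the definition. The documents should say whether solid food is part of the criterion.

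**What to change.** 1. Add a daily yes/no item for enteral nutrition beside the parenteral and oral items, or confirm in the protocol that the CRF records the day enteral feeding ended.
2. Align the stop rules in Sections 11 and 14.1, the synopsis questions and the Section 14.2 entry with Sections 7.1.1 and 12.1. Recording then continues until the first day with no parenteral nutrition, no enteral nutrition and at least three oral intakes, or until day 15.
3. State that the synopsis variable for time until full oral nutrition uses this same criterion, so that there is one date and one rule.
4. Say whether solid food is part of the criterion or only part of the endpoint's name.

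The cost is at most one CRF item, wording changes in those places and, for affected patients only, further days of a check already made daily, up to day 15. Nutritional management does not change.

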### **Unauthorised concomitant medication:**

Aside from basal fluid administration no other colloid or crystalloid volume replacement agents than study medications will be applied *during surgery* as long as Investigational Product as compiled by the pharmacist is available, with the exception of concentrated electrolytes for individual corrections.

On ICU if volume replacement with colloidal is required on the day of surgery no HES-product but other colloidal solutions (e. g. gelatine) will be used.

